#### Sampling, settings and research participants

Families who have attended FGCs will be identified by local authorities–we will work with several large authorities in England, and access anonymised data from the Department for Education, NHS Digital and the Office for National Statistics (ONS). This part of the study is not linked in any way to the WP2 families. In these participating local authorities, we will also access routine data on families who have been referred to children’s services but have not had an FGC, in order to delineate the circumstances in which families do and do not take part in FGCs in these particular authorities.

A comparison group of local authorities which do not offer FGCs will be identified in the WP1 survey. Families from these authorities will be identified from the Children in Need Census. This part of the study uses data from only one UK country–England–because the datasets are different for each nation and given the complexity of data linkage it would not be feasible to attempt this study in more than one nation. We have chosen England as having the largest population.

Eligible families will be those with at least one child under 18 years of age referred to departments of Children’s Social Care Services from 1.1.17 to 31.12.19 at participating local authority sites in England (there is no intention to connect these local authorities to those taking part in earlier work packages). No additional exclusion criteria will be applied. At this stage we are not imposing a lower age limit. However, although we are confident that linkage to health records for school-age children is viable, there is some uncertainty about this linkage for pre-school children. We will therefore have to test the feasibility of extending the age profile to include all children from birth, in the early stages of WP3.

To make the two groups of families from different local authorities comparable for analysis, we will use statistical techniques to improve balance across the two groups for several known confounders. We will use propensity score weighting [40, 41] to estimate the average ‘causal’ effect of having an FGC on the outcomes.

A realistically achievable sample size of 300 families who have had an FGC and 1000 ‘control’ families in local authorities that do not offer FGCs would allow for the detection of a difference of 10.5 percentage points between groups for a binary outcome in a ‘worst-case scenario’ (i.e. proportions around 0.5) with 90% power and 95% confidence (two-sample test for proportions), but since propensity score weighting tends to shrink the ‘effective’ sample size the minimum detectable difference will be somewhat larger.

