## Introduction

A family group conference (FGC) in child welfare brings immediate and wider family members, and others from their social network, together to decide on the best way to meet the needs of a child who requires support and/or protection. Unlike professionally led meetings, FGCs aim to shift decision-making to family members. They do so more fully than attempts to make traditional case conferences more strengths-based [1]. Staff who are termed ‘co-ordinators’ prepare potential attendees for the FGC meeting and usually facilitate the start of the meeting, but then professionals leave the room so that family network members only can have ‘private family time’ [2]. Children and young people sometimes attend themselves, but this depends on age and the family situation [3]. Sometimes children and young people are represented by advocates. FGCs originated in Aotearoa New Zealand, with a focus on Māori whanau (families) and in the context of concern about the over-representation of Māori tamariki (children) in state child welfare interventions [4].

There is also concern in many other countries about rising levels of state intervention, especially rising rates of children in out-of-home care [5]. There is concern about a professionally led child protection system which can be confrontational in style [6] and focused on forensic investigation at the expense of support for families [7]. In this context, FGCs are often seen as an important element of developing a child welfare system that is based on more positive relationships between the state and vulnerable families [8].

FGCs have the two primary aims of increasing family participation in important decisions about children and reducing more intrusive state intervention.

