### Work Package 3: Comparison of service use and associated costs in FGC participants and a comparison group after two years using a quasi-experiment (RQ4)

Public-facing title: Service use study (Family VOICE project)

WP3 is a quasi-experiment to assess service use outcomes of FGCs and the economic dimension of these. The experimental dimension is comparison of families who have had FGCs with similar families in local authorities with no FGC provision. This work package will assess some longer-term outcomes from the programme theory developed in WP1 for which administrative data are more suitable than self-report, because of the need for complete coverage of the relevant population without social desirability bias.

Outcomes to be measured include:

1. Primary outcome

The primary outcome is whether category (of seriousness) of children’s social care intervention at two years after FGC (or equivalent date for comparison group) is the same level, lower or higher than at the time of FGC. A ladder of escalation will be used, with state intervention categories ordered from most to least serious, including the child having been:

categorised as in need (and reason for this);subject to a child protection investigation;on a child protection plan;looked after by the local authority (and, if so, on what legal basis; type of care–foster, kinship, residential, placed with parents).

The primary outcome variable will be binary, describing whether the category of statutory intervention at 2 years after FGC (or equivalent date for the non-FGC group) is the same or lower than at the time of FGC (or equivalent date) or whether it is higher.

2. Secondary outcomes

Highest category of children’s social care intervention since the FGC (or equivalent date for comparison group) at any time during the two-year follow-up.

A summary measure of duration and seriousness of all children’s social care intervention during follow-up.

Health care use for health conditions and events which might potentially be affected by FGC attendance–e.g., child and parent mental health, serious injury to a child, assault resulting from domestic abuse:

hospital admissions;outpatient appointments;‘Improving Access to Psychological Therapies’ [39] services;community mental health services;accident and emergency attendances.

Absence from school and special educational needs provision.

Incremental cost per adverse social-care-outcome-adjusted year avoided.

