#### Data analysis

We will use Stata or R software to estimate a family’s propensity for having an FGC with a logistic regression on variables including stage of the child welfare process (referral, child in need, child protection assessment, child protection plan), reason for referral and family demographics. The analysis model for the primary outcome variable (whether the level of social care intervention at two years after the FGC–or equivalent baseline date for the control group–has increased or not) will be two-level logistic regression, with random effects for local authorities and weighting of families according to their propensity for having an FGC. Fixed effects will include intervention (whether a family has had an FGC or not) as well as other factors–to be determined in WP1 –to account for the different ways FGCs are set up in different local authorities. Effect estimates will be presented with two-sided 95% confidence intervals and p-values. Secondary outcomes will be analysed using the same propensity score weighting approach and appropriate two-level regression models depending on the type of outcome variable (e.g., logistic for binary outcomes, linear for continuous outcomes).

We will undertake multiple imputation to explore the impact of potential missing data. We will also consider alternative covariate balancing or matching methods, such as entropy balancing [43], Mahalanobis distance matching [44] and coarsened exact matching [45] if propensity score weighting does not achieve good enough covariate balance and/or as sensitivity analyses. Detailed statistical analysis plans for WP2 and WP3 will be finalised prior to any analysis being performed, and these will be published on the study website.

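### WP3 selects the FGC group on attendance but applies no matching step to the comparison group, so the primary contrast may carry a selection bias that the named propensity variables cannot remove

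*Protocol article*

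**What the plan says.** All references are to the Protocol article, Work Package 3, unless stated.

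- **Contrast.** The opening of Work Package 3 describes a "comparison of families who have had FGCs with similar families in local authorities with no FGC provision".
- **Exposed group.** Under Sampling, settings and research participants: "Families who have attended FGCs will be identified by local authorities".
- **Comparison group.** Same section: "Families from these authorities will be identified from the Children in Need Census". Eligibility on both sides is referral to children's social care in 2017-19 with at least one child under 18, and "No additional exclusion criteria will be applied".
- **Families without an FGC in provider authorities.** Their routine data are accessed "in order to delineate the circumstances in which families do and do not take part in FGCs in these particular authorities". No role in the effect estimate is described for them.
- **Target.** Propensity score weighting is used "to estimate the average ‘causal’ effect of having an FGC on the outcomes".
- **Weighting model.** Data analysis names "variables including stage of the child welfare process (referral, child in need, child protection assessment, child protection plan), reason for referral and family demographics". Entropy balancing, Mahalanobis matching and coarsened exact matching are alternatives or sensitivity analyses.
- **Start of follow-up.** The primary outcome runs from the FGC, or an undefined equivalent date for the comparison group. Data collection and linkage instead follows children for two years from referral.
- **Limitation.** The Discussion admits possible baseline differences in unmeasured confounders in WP3. It does not name selection on attendance.

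**The concern.** Attending a conference happens some time after referral and is not automatic. The Introduction says that co-ordinators "prepare potential attendees for the FGC meeting", so a preparation phase precedes the meeting. The WP2 Data collection section adds that attendance is hard to predict and that family dynamics before a conference are often difficult. Whether a family gets as far as a conference plausibly depends on willingness, on having a network to convene, and on how the case develops in the meantime. The same things plausibly affect later escalation, which is the primary outcome.

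The FGC group is filtered on this step and the comparison group is not. No conference was on offer in the comparison authorities, so the counterparts of families who would not have attended cannot be recognised there. Weighting and matching balance only what is measured, and none of the named variables measures the filter. A difference in escalation could then reflect who reaches a conference rather than what the conference does.

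**Working it through.** **1. The plan's own figure.** Inputs from the sample-size paragraph: 300 FGC families, 1000 control families, proportions around 0.5, 90% power, 95% confidence. The Data analysis section gives two-sided intervals.

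Detectable difference = (1.960 + 1.282) × √[0.25 × (1/300 + 1/1000)] = 3.242 × 0.0329 = 0.107, or 10.7 points. Solving for power with one proportion fixed at 0.5 gives 10.6 points. In the other direction, 10.5 points with 300 and 1000 families gives 89.3-89.7% power. The stated 10.5 points is reproduced to within rounding, so the sample size is not at fault.

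**2. Size of the possible bias.** Let q be the share of families referred to an FGC service who do not attend. Let r_N and r_A be the two-year escalation risks of non-attenders and attenders. Suppose the FGC has no effect and weighting makes the comparison group resemble the full referred mix:

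- FGC group risk = r_A
- comparison group risk = (1 − q) × r_A + q × r_N
- spurious difference (comparison minus FGC) = q × (r_N − r_A)

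The gap r_N − r_A must be read as what remains after weighting. The protocol gives neither q nor the gap, so both are assumed. The table shows percentage points; a positive value means the FGC looks protective.

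| q | gap −10 | gap 0 | gap +10 | gap +20 | gap +30 |
|---|---|---|---|---|---|
| 10% | −1 | 0 | 1 | 2 | 3 |
| 20% | −2 | 0 | 2 | 4 | 6 |
| 30% | −3 | 0 | 3 | 6 | 9 |
| 40% | −4 | 0 | 4 | 8 | 12 |
| 50% | −5 | 0 | 5 | 10 | 15 |

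**3. Chance of a significant result with no true effect** (300 v 1000, comparison risk 0.5, ignoring clustering and loss of effective sample size from weighting):

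- 2 points (q = 20%, gap 10): about 9%
- 6 points (q = 30%, gap 20): about 45%
- 12 points (q = 40%, gap 30): about 96%

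**4. Why the sign is open.** The primary outcome is change from the category at time zero. Take a child who becomes looked after before a conference could be held.

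- If time zero is the equivalent date and falls after that event, the comparison counterpart starts at the most serious category listed. The case counts as same or lower, not as escalation.
- If time zero is referral, the same event counts as escalation in the comparison group. The FGC group, by construction, contains only families who got as far as a conference.

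The two sections therefore imply different biases from the same selection. Families whose problems settle before a conference also drop out of the FGC group, which pushes against the FGC.

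**The case against.** The strongest points on the other side are these.

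- **Direction.** A reader might infer that the design makes FGCs look protective even if they do nothing. The documents do not support that. Step 4 shows how early breakdown can sit in the baseline category, and families who improve early are lost too. This objection stands.
- **Size.** A reader might take one favourable range of bias as the likely one. The protocol supplies no inputs, and weighting on stage and reason for referral probably absorbs part of any deterioration. This stands, so the table is a range and not an estimate.
- **Completers against everyone.** That would misdescribe the design. Comparison families are weighted to resemble FGC families, and the covariate list is open. This stands for measured variables. It does not help with willingness or network, which leave no trace where no FGC was offered.
- **Missing data fields.** A reader might infer that the extract cannot identify non-attenders. The article lists no extract fields and leaves the linkage model to WP1, so that is not shown.
- **Already acknowledged.** The Discussion admits unmeasured confounding, and detailed plans are deferred. This stands in part. But who is in the exposed group is fixed here, and a later analysis plan cannot use an attended flag that was never requested.
- **Redefining the main contrast as all referred families.** This would replace the stated target and dilute the effect. With 300 attenders and q of 20-40%, the referred group is 300/(1 − q) = 375 to 500. A true 10.5-point effect in attenders becomes 10.5 × (1 − q) = 8.4 to 6.3 points. Power falls from about 89% to about 79-63%. Nor would it restore full symmetry, because comparison authorities have no referral to an FGC service. This stands, and it argues for a sensitivity analysis, not a new main contrast.

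**Conclusion.** The one-sided selection is real and is fixed by the text: attendance defines the FGC group, no equivalent step defines the comparison group, and neither the named covariates nor the alternative balancing methods measure what drives attendance. The primary contrast may therefore be biased, plausibly but not certainly in favour of FGCs.

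Under the assumed shares and residual gaps, the spurious difference runs from −5 to +15 points. It could be trivial or could exceed the 10.5-point detectable difference, and the documents cannot say which. The documents do not support a firm claim that the FGC will look protective, or any single figure for the bias. The conclusion rests on attendance being related to escalation risk after weighting, which is plausible but not documented.

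**What to change.** 1. Keep the effect of having an FGC as the main contrast.
2. Ask provider authorities, where records exist, to identify all families referred to the FGC service in 2017-19, with date of referral to that service, attended yes/no, and FGC date.
3. Pre-specify a key sensitivity analysis comparing all families referred to the FGC service, attended or not, with weighted comparison families.
4. If the flag cannot be obtained, compare all FGC-eligible families in provider authorities, using the routine data already to be accessed there, with comparable families in non-provider authorities.
5. Name selection on attendance as a WP3 limitation, and state that a benefit seen only in the attended contrast will be interpreted with caution.
6. Define the equivalent date and reconcile the start of follow-up between the outcome list and Data collection and linkage, since the bias depends on it.

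Cost: a few extra fields in a historical extract, which some authorities may not hold, and one more run of the weighted model. The sensitivity contrast is diluted and less powerful (about 79-63% under the assumptions above), so a null result there does not by itself refute an effect in attenders. Selection into FGC referral remains.

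### The WP3 detectable difference of 10.5 points assumes independent families; clustering by local authority enlarges it beyond the acknowledged weighting loss, by an amount the protocol's inputs do not fix

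*Protocol article*

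**What the plan says.** The WP3 section on sampling, settings and research participants starts from "A realistically achievable sample size of 300 families who have had an FGC and 1000" control families. It states that these numbers "would allow for the detection of a difference of 10.5 percentage points between groups for a binary outcome", taking a worst case for the event rate ("i.e. proportions around 0.5"), "with 90% power and 95% confidence (two-sample test for proportions"). Its one caveat is that propensity weighting reduces the effective "sample size the minimum detectable difference will be somewhat larger".

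The opening of Work Package 3 defines the experimental contrast as "comparison of families who have had FGCs with similar families in local authorities with no FGC provision". The sampling section takes FGC families from an unspecified number of large English authorities, and comparison families from authorities that the WP1 survey shows to have no FGC service. Referred families in provider authorities who had no FGC are used only to describe who does and does not take part.

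The WP3 data analysis section says the primary model "will be two-level logistic regression, with random effects for local authorities and weighting of families according to their propensity for having an FGC". It adds: "Effect estimates will be presented with two-sided 95% confidence intervals and p-values".

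**The concern.** A two-sample test for proportions treats all 1300 families as independent. In the primary contrast, every FGC family belongs to a provider authority and every control to a different, non-provider authority. The FGC effect is therefore estimated wholly between authorities, and any variation in escalation rates from one authority to another enters its standard error, as it would in a cluster-allocated study. The analysis section allows for such variation through the random effects; the sample size statement does not.

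The weighting caveat does not cover this. Weighting lowers the effective number of families because their weights are unequal, whereas clustering lowers it because families in the same authority resemble one another. The two losses are separate and both apply.

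This is the only power statement for the primary outcome of the comparative work package. A reader who takes 10.5 points, plus a little for weighting, as the study's resolution would expect more precision than the design may give. The worst-case label could strengthen that impression, although it refers only to the event proportion.

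**Working it through.** **Inputs from the protocol:** 300 FGC and 1000 control families; proportions around 0.5; 90% power; 5% significance, two-sided (sidedness from the WP3 data analysis section).

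**Inputs not given, so assumed:** the ICC for the binary outcome, and the number of authorities in each group. ICCs of 0.005 to 0.05 are used, with 6 provider and 20 comparison authorities, or 10 and 30.

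**Step 1: reproduce the stated figure.** With variance 0.25 in both groups,

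SE = √[0.25 × (1/300 + 1/1000)] = 0.0329

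Detectable difference = (1.960 + 1.282) × 0.0329 = 10.7 points.

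Pooled-variance calculations give 10.56 to 10.63 points, and an unpooled variance with the control group at 0.5 gives 10.49. Under the pooled formula, power for 10.5 points is 89.3% to 89.7%. So 10.5 points at 90% power is right for independent, unweighted families.

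**Step 2: add clustering.** With m families per authority, each group's variance is multiplied by its design effect,

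DE = 1 + (m − 1) × ICC

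SE = √[0.25 × (DE₁/300 + DE₂/1000)]

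Detectable difference = 3.2415 × SE; power for 10.5 points = Φ(0.105/SE − 1.960).

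Worked case, 6 and 20 authorities, ICC 0.01: m = 300/6 = 50 and 1000/20 = 50, so both design effects are 1 + 49 × 0.01 = 1.49. Then SE = 0.0329 × √1.49 = 0.0402. The detectable difference is 13.0 points and power is Φ(0.105/0.0402 − 1.960) = 74%.

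**Results (normal approximation, proportions near 0.5, before any weighting loss)**

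| Assumed ICC | 6 + 20 authorities: difference | Power for 10.5 points | 10 + 30 authorities: difference | Power for 10.5 points |
|---|---|---|---|---|
| 0.005 | 11.9 | 82% | 11.4 | 85% |
| 0.01 | 13.0 | 74% | 12.2 | 80% |
| 0.02 | 15.0 | 62% | 13.5 | 71% |
| 0.05 | 19.8 | 40% | 16.8 | 52% |

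The same formula with variance 0.25 and an ICC of zero gives 10.7 points and 89% power, which is the fair baseline for this table.

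**Step 3: the favourable end.** With an ICC of 0.001 and 10 + 20 authorities, the difference is about 10.8 points and power is 88%, so the loss is negligible.

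**Step 4: scale of the assumption.** At a proportion of 0.5, an ICC of 0.01 corresponds to a between-authority standard deviation of √(0.01 × 0.25) = 0.05, that is, 5 percentage points.

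**Step 5: weighting, separately.** As an illustration only, if weighting cut the effective control group from 1000 to 300, with no clustering, the difference would be 3.2415 × √[0.25 × (2/300)] = 13.2 points.

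**The case against.** Several counter-arguments have force.

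- **No calculation is wrong.** The protocol names its test and the figure reproduces. This stands: the fault is an omitted design effect, not an arithmetic slip.
- **The protocol already says 10.5 points is optimistic.** The same sentence concedes a larger detectable difference. This also stands, but the concession is tied to weighting alone.
- **The event rate may be away from 0.5.** If, as an assumption, about 20% of families escalated, the variance would be 0.16 instead of 0.25 and every difference above would shrink by √(0.16/0.25) = 0.8; the 13.0 points would become about 10.4. The independent figure shrinks by the same factor (10.7 to about 8.5), so the relative loss from clustering is unchanged.
- **The residual ICC may be low.** Weighting on stage, referral reason and demographics, and an outcome defined relative to the family's own baseline category, could both reduce it. By how much is unknown.
- **The group sizes are minimums in the abstract.** That is so, but extra families in the same authorities help little. With 6 + 20 authorities and an ICC of 0.02, unlimited families per authority still give 3.2415 × √[0.25 × 0.02 × (1/6 + 1/20)] = 10.7 points.
- **The analysis itself handles clustering.** The random effects are planned and confidence intervals will be reported, so an imprecise null should show as a wide interval.

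A reader might infer that WP3 is badly underpowered, or that a null result will be misread as excluding 10.5 points. The documents support neither. The first depends on an ICC and authority numbers that the protocol does not give, and nothing in it says a null would be interpreted that way.

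**Conclusion.** The sample size statement does not match the protocol's own design and primary model. The 10.5 points at 90% power applies to independent, unweighted families, and clustering by authority is a further, unstated loss. The direction is certain for any ICC above zero.

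The size is conditional. Under the assumptions tabulated above, the detectable difference runs from about 11.4 to 19.8 points; with an ICC near 0.001 and many authorities it barely moves. These figures take proportions near 0.5, equal numbers of families per authority within each group, a normal reference distribution and no weighting loss.

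It would be loose to say that FGC exposure is fixed by authority in general, since some referred families in provider authorities have no FGC. The statement holds for the primary contrast, which does not use those families as controls.

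**What to change.** Reword the WP3 sample size paragraph to do three things:

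1. Label 10.5 points as the figure for independent, unweighted families.
2. Say that clustering by local authority and propensity weighting each enlarge it.
3. Give a short table of detectable differences over a stated range of ICC, authorities per group and effective sample size after weighting, marked as assumptions where no data support them.

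The cost is text only, and the stated detectable difference becomes less favourable. The choice of small-sample degrees of freedom for the FGC effect can be left to the statistical analysis plan. How many authorities to recruit is a feasibility decision and not part of this correction.
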